#### Follow-up assessment

During the last week of the 12-week intervention period, all participants will be approached by the trial coordinator to arrange an appointment for a follow-up assessment within seven days post-intervention. Similar to the baseline assessment, participants will be instructed to attend ISH on a separate day after the intervention has ended to have their follow-up assessment following the procedures detailed above. The participants will also be issued the combined set of valid and reliable self-reported outcome questionnaires used pre-intervention.

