##### Anthropometry

The following anthropometric/body composition variables will be collected (body mass index [BMI], body weight [BW], body fat percentage [%BF], waist circumference [WC], lean mass [LM], fat-free mass [FFM], waist-hip ratio [WHR], height). All outcomes will be measured using standard procedure with participants dressed in light, close-fitted clothes and with bare feet. Height, WC and BW will be measured to the nearest 0.1cm and 0.1kg respectively using a calibrated scales, stadiometer and tape measure respectively. Waist circumference will be recorded midway between the top of the pelvic bone and the bottom margin of the last rib using a tape measure [52]. Whole body composition will be measured using a bioelectrical impedance body composition analyser (seca mBCA 515).

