##### Aerobic

This intervention consists of 3 × 50-min sessions per week of progressive continuous aerobic exercise, completed on a cross-trainer or stationary bike or combination of both. Over the course of weeks 1 to 6, session length will gradually increase (in 5-min blocks) until participants can perform 3 × 50-min sessions in week 7. The programme will progressively increase in intensity from weeks 1 to 12 (Table 3), starting at an intensity of 40–50% HRR (weeks 1–2) and finishing at an intensity of 75–80% HRR (weeks 11–12). Participants will wear heart rate monitors and use the RPE scale to monitor intensity levels (make: Garmin; model: Forerunner 45).

**Table 3 Tab3:** Progression plan from week 1 to week 12 for all exercise groups

Summary description of exercise interventions [frequency, intensity, time and type (F.I.T.T.)]						
Trial arm	Weeks 1–2	Weeks 3–4	Weeks 5–6	Weeks 7–8	Weeks 9–10	Weeks 11–12
Aerobic	3 sessions/week Low Intensity (40–50% HRR)^a^ Continuous aerobic exercise 20–30 min^b^	3 sessions/week Low–moderate intensity (50–55% HRR)^a^ Continuous aerobic exercise 30–40 min^b^	3 sessions/week Low–moderate Intensity (55–60% HRR)^a^ Continuous aerobic exercise 40–50 min^b^	3 sessions/week Moderate intensity (60–70% HRR)^a^ Continuous aerobic exercise 50 min	3 sessions/week Moderate–vigorous intensity (70–75% HRR)^a^ Continuous aerobic exercise 50 min	3 sessions/week Vigorous intensity (75–80% HRR)^a^ Continuous aerobic exercise 50 min
Resistance	3 sessions/week Low load (40–50% 1-RM)^a^ Resistance training 20–30 min^b^ 2 × 12 reps (6 exercises)	3 sessions/week Low–moderate load (50–55% 1-RM)^a^ Resistance training 30–40 min^b^ 3 × 12 reps (6 exercises)	3 sessions/week Low-moderate load (55–60% 1-RM)^a^ Resistance training 40–50 min^b^ 3–6 × 12 reps (6 exercises)	3 sessions/week Moderate load (60–65% 1-RM)^a^ Resistance training 50 min; 3–6 × 12 reps (6 exercises)	3 sessions/week Moderate–high load (70–75% 1-RM)^a^ Resistance training 50 min; 3–6 × 12 reps (6 exercises)	3 sessions/week High load (75–80% 1-RM)^a^ Resistance training 50 min; 3–6 × 12 reps (6 exercises)

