##### Control

The control group will be instructed to maintain their physical activity levels for the 12-week intervention period. After this period, all participants randomised to the control group will be offered the opportunity to join one of the three exercise groups as per their preference to avail of an individualised and supervised exercise programme for 12 weeks.

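### The follow-up window lets exercise-arm participants be tested the day after a peak-load session, while controls have no session to recover from

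*Protocol article*

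**What the plan says.** **Visit timing (Methods, Follow-up assessment).** Booking takes place in week 12 for every arm: "During the last week of the 12-week intervention period, all participants will be approached by the trial coordinator" in order to "arrange an appointment for a follow-up assessment within seven days post-intervention". The same section adds that "participants will be instructed to attend ISH on a separate day after the intervention has ended to have their follow-up assessment". It gives no minimum number of hours or days since the last session.

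**Training at that point (Aerobic, Resistance, Table 3).** Weeks 11–12 carry the highest prescribed intensity and load: 75–80% HRR, 75–80% 1-RM, or both in the combined arm. Each resistance exercise may run to six sets.

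**What is tested.** The visit repeats the baseline procedures. Muscular strength comprises a 5RM bench press and maximal pulls on the leg and grip dynamometers. The treadmill test (Cardiorespiratory fitness) stops at 85% of age-predicted maximum heart rate, at RPE 18 or above, or at volitional exhaustion. VO2 max is then computed from speed and grade.

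**Controls (Control).** Controls are asked to keep their activity at its usual level for the 12 weeks. On what happens next, the article says: "After this period, all participants randomised to the control group will be offered the opportunity to join one of the three exercise groups".

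**Use of the results.** Aims and objectives makes the between-group differences at 12 weeks secondary, and says the pilot data will support a power calculation. Sample size names CRF as the primary outcome of the later trial.

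**The concern.** Carry-over from the last session can occur only in the arms that had a last session. Randomisation does not balance it, because it is a consequence of allocation. Participants enter physically inactive and controls stay so. Neither the baseline visit nor the control follow-up is therefore likely to be preceded by a comparable session.

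A tired or sore participant may lift less. If fatigue raises heart rate or perceived exertion, she also reaches a treadmill stopping criterion at a lower grade, and the equation returns a lower VO2 max. Both effects would pull the exercise arms towards control.

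The effect could also differ by mode, which matters for the secondary hypothesis. In the sample plan (Table 5), the third session of both weeks contains barbell deadlift, a lunge and triceps work, and these load muscle groups that the dynamometer and bench press then test.

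What is at stake is a modest, avoidable understatement of effect in data meant to help size the next trial, plus some added variance from the choice of appointment day.

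**Working it through.** The plan gives no figure on this point to reproduce. The check sets the timing statements side by side and bounds what they allow.

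**1. Earliest permitted test.** The limits are a separate day (lower) and seven days (upper), so days 1 to 7. The article does not say whether day 0 is the last session or the calendar end of week 12. Let g be the number of days from the last session to day 0. The interval from last session to test is then g + 1 to g + 7 days. Since g = 0 is possible under either anchor, next-day testing is allowed under both.

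**2. Share tested within two days of a session.** Assume appointments are spread evenly over the seven days (the documents do not say this).

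- g = 0: 2/7 = 28.6%
- g = 1: 1/7 = 14.3%
- g = 2 or more: 0%

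With 60/4 = 15 per arm and 20% attrition, the three exercise arms have 45 × 0.8 = 36 completers. At g = 0 that gives 36 × 2/7 = 10.3 women; at g = 1 it gives 5.1. For the resistance and combined arms alone, 30 × 0.8 = 24 and 24 × 2/7 = 6.9.

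**3. Shift in an arm mean.** Assume a 5–10% acute strength loss in those women (no source in the documents). At g = 0, 0.286 × 5% = 1.4% and 0.286 × 10% = 2.9%. At g = 2 the shift is zero. The range is thus 0 to 2.9%, and every step of it is assumed.

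**4. Against the pilot's precision.** The standard error of a difference between two arms, in SD units, is √(2/n): √(2/15) = 0.37, or √(2/12) = 0.41 after attrition. An assumed shift of 0.1–0.3 SD would be 0.1/0.41 = 0.24 to 0.3/0.37 = 0.8 of a standard error.

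**5. What attenuation would do downstream (illustration only).** Required size varies as 1/effect². If the later trial were sized on the pilot effect, a 5% attenuation would turn the stated 484 into 484/0.95² ≈ 536, and a 10% attenuation into 484/0.90² ≈ 598.

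**6. Controls.** The exercise offer and the follow-up window both run from the end of the 12 weeks, and the text does not state their order. At worst, a control who started at once and was tested on day 7 would have had 3 of 36 sessions (8.3%). These would be introductory sessions of 20–30 minutes, 60–90 minutes in all. The full aerobic schedule in Table 3 totals 6 × (20+30+40+50+50+50) = 1440 to 6 × (30+40+50+50+50+50) = 1620 minutes, so the overlap is 60/1620 = 4% to 90/1440 = 6% of it.

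**The case against.** **Operational detail.** Rest instructions before testing often sit in a full protocol or assessment manual, and an article may omit them. This stands as a caution, and it is one reason to rate the point low. It does not dispose of the point, because the article itself states the visit window, and that window as written admits next-day testing.

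**Load and test type.** Load rises as tolerated, so not every participant will have trained at the block's maximum. The treadmill test is submaximal. Questionnaires can be completed online before or after the visit, so the visit day does not fix when pain is reported. All of this is fair, and it weakens the case for pain and, to a degree, for VO2 max more than for strength.

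**Size.** The outcomes are secondary, and sampling error at 12–15 per arm would probably exceed any bias. This also stands.

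**Control contamination.** A reader might infer that controls will already be exercising when they are assessed. The text does not support that. Assessment is booked during week 12 and the offer comes only afterwards, so the natural reading puts assessment first. The programme is supervised, so a control cannot begin without the trial team. The flow and schedule figures, which may show the order, are not visible in this copy. Only an unstated order remains.

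**Conclusion.** The point holds as a weakly set lower limit. Exercise-arm participants may be tested from the day after a session in the highest-load block, and controls have no counterpart. If carry-over occurs, it follows allocation and most plausibly shrinks the exercise-versus-control differences in strength and predicted VO2 max.

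The size is not established. A reader might take 29% of exercisers affected, or a 1.4–2.9% fall in mean strength, as estimates. They are not: they rest on an even spread of appointments, on the last session being day 0, and on a strength loss the documents do not give. Moving the anchor by two days takes them to zero.

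The primary aim, feasibility and acceptability, is untouched. This is a low-cost improvement, worth making because the CRF data are meant to inform the definitive trial.

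**What to change.** In Follow-up assessment, keep the seven-day upper limit and add a minimum interval between the last exercise session and testing. One example is to book on days 3–7 counted from the last session, with the matching calendar window for controls. The documents do not dictate day 3; what matters is that a minimum is stated and is the same for all exercise arms. Apply the same no-exercise interval before the baseline visit, and record the days from last session to test so that the spread can be reported.

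In Control, add one clarifying sentence: the optional programme starts after the follow-up tests and questionnaires are complete.

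The cost is scheduling wording and one extra recorded item. In the example, bookable days fall from seven to five, which may make a few appointments harder to place. No visits, participants or analyses are added.

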### Qualitative study

All participants randomised to the exercise interventions will be provided an exit questionnaire and invited to participate in a semi-structured telephone interview (or face-to-face interview if preferred/convenient) within two weeks of completing their follow-up assessment. The exit questionnaire was internally developed specifically for this study and will explore participants perception of the intervention including topics such as the randomisation process, intervention design (i.e. number of sessions etc.) and satisfaction with the intervention. We aim to conduct a minimum of 18 (6 per exercise group) semi-structured interviews. Interviews will take approximately 30–40 min. Participants who consent to take part in an interview will either be contacted by phone at their convenience or invited to attend ISH for a face-to-face interview and will discuss a predetermined set of topics. These topics will be guided by the theoretical framework of acceptability (TFA) domains [68] and will include reasons for participation in the trial, their understanding and the acceptability of the trial procedures, their experiences and feelings around the exercise programmes, their expectations and satisfaction with the programmes, the barriers/motivators to participation in the trial/exercise in general, self-efficacy, changes to lifestyle, behaviours, beliefs or feelings following participation in the trial and the likelihood of continuing participation in exercise. The interview sessions will be audio-recorded and then transcribed verbatim for analysis of themes.

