**Methods and analysis:**

Sixty women (aged 18–50) with obesity (body mass index [BMI] ≥ 30 and/or waist circumference ≥ 88 cm) who are physically inactive, have no unstable health conditions and are safe to exercise will be recruited from September 2021 to December 2022. The main outcome will be feasibility and acceptability of the intervention and procedures. Trial feasibility outcomes will be evaluated to determine if a definitive trial should be undertaken. Trial acceptability will be explored through follow-up qualitative interviews with participants. Secondary outcomes will include CRF (predicted VO_2_ max), anthropometrics (i.e. BMI), strength (5RM bench press, leg dynamometry, grip strength) and other health outcomes (i.e., pain). Participants will be block randomised into one of four trial arms (aerobic exercise, resistance training and combined training groups, non-active control group) and measurements will be completed pre- and post-intervention. The exercise groups will receive an individualised supervised exercise programme for 3× sessions/week for 12 weeks. The change in mean values before and after intervention will be calculated for primary and secondary outcomes. ANOVA and *t*-tests will be applied to evaluate within-group and between-group differences. If sufficient participants are recruited, the data will be analysed using ANCOVA with the age and BMI as covariates.

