### Aims and objectives

Therefore, the primary aim is to evaluate the feasibility and acceptability of prescribed time-matched aerobic, resistance and combined interventions (targeting changes in cardiorespiratory fitness) in women with obesity and to inform whether a future definitive trial could or should be undertaken. We will assess recruitment challenges; retention rates, attendance rates and adherence of participants to prescribed programme, incidence of adverse events and participant’s experience of the intervention and the acceptability of trial procedures and the programmes. We will also collect data from which a power calculation can be based to determine the number of participants needed per group in order to achieve significance in a potential follow-up randomised controlled trial (RCT).

The secondary objectives are to determine the mean difference between groups (three exercise groups and a non-exercise control group) at 12 weeks in:(i)CRF (predicted VO_2_ max)(ii)anthropometric outcomes (Body mass index (BMI), percentage body fat (%BF), lean mass (LM), fat mass (FM), waist-hip ratio (WHR) and waist circumference (WC)(iii)strength (five repetition maximum [5RM] bench press, leg dynamometry, grip strength)(iv)self-reported quality of life, physical activity, sedentary time, sleep, mood and pain

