#### Statistical methods

To evaluate the feasibility of the intervention, the number of eligible participants recruited, randomised and retained as well as dropouts lost to follow-up will be analysed as percentages. Data on participants attendance adherence to and compliance with prescribed interventions (i.e. average adherence to reps, sets, HR) will be analysed and the mean results reported as percentages. The incidence of adverse events (an adverse event defined as an event which a participant identifies a problem caused by the exercise programme that required the participant to seek treatment from a health professional and/or prevents participation in the programme) will also be analysed as percentages across all interventions. The acceptability of trial procedures based on participants’ experiences will be explored qualitatively as outlined in this protocol below. Feasibility data will be used to inform the development of a potential full-scale RCT.

In line with CONSORT guidance, the analysis of secondary outcomes will be conducted on an intention to treat basis. All data collected from participants (sociodemographic information, outcome questionnaire scores etc.) will be coded, cleaned and checked for errors. The data will then be entered into the Statistical Package for the Social Sciences (SPSS Version 26) for analysis. The study’s statistician ([name]) will remain blinded to group allocation until the analysis is complete. The change in mean values before and after intervention will be calculated for secondary outcomes. Analysis of variance (ANOVA) and *t*-tests will be applied to compare between-group and within group-differences at baseline and follow-up for each outcome. If there are sufficient participants (*n* = 60), the data will be analysed using analysis of covariance (ANCOVA) with the age and BMI as covariates. Statistical significance will be defined as *p* ≤ 0.05.

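### Acceptability of trial procedures is part of the main outcome, but the control arm is never asked about it, and no route is described to exercise-arm women lost to follow-up

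*Protocol article*

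**What the plan says.** The Abstract (Methods and analysis) states: "The main outcome will be feasibility and acceptability of the intervention and procedures". Aims and objectives repeats the double target, the procedures as well as the exercise: "participant’s experience of the intervention and the acceptability of trial procedures and the programmes".

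Statistical methods passes the acceptability of procedures to the qualitative part: "The acceptability of trial procedures based on participants’ experiences will be explored qualitatively as outlined in this protocol below". No other source of acceptability data is named.

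The Qualitative study section then defines who is asked: "All participants randomised to the exercise interventions will be provided an exit questionnaire and invited to participate in a semi-structured telephone interview", timed "within two weeks of completing their follow-up assessment". It sets a minimum of 18 interviews, six per exercise group, and none for controls. The questionnaire covers perceptions of the intervention, "including topics such as the randomisation process, intervention design (i.e. number of sessions etc.) and satisfaction with the intervention". The interview topics also include understanding and acceptability of the trial procedures. Under Data analysis (qualitative), the share of participants choosing particular Likert statements is to be reported alongside the themes.

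**The concern.** The target covers the trial's procedures, but the women asked about them come from three of the four arms. The missing arm is the one whose experience of those procedures differs most. Controls are randomised, attend both assessments and are told to keep their activity unchanged for 12 weeks before being offered a programme. Whether women find that allocation tolerable bears directly on the pilot's question of whether a definitive trial with such a control arm should follow. Only women who were allocated supervised training will give a view on randomisation.

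A second, softer gap concerns exercise-arm women who do not return. If completing the follow-up assessment is what prompts the contact, a woman lost to follow-up never reaches that point. Her reasons for leaving are then not collected.

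A statistical analysis plan could not repair either gap, because the data would not exist.

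**Working it through.** **Inputs (all from the protocol article)**
- Trial design: allocation 1:1:1:1.
- Sample size: 484 for a definitive trial, pilot at about 10% of that, 20% attrition, target 60.
- Qualitative study: both instruments limited to the exercise arms; at least 18 interviews.

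**The plan's own figure**
- 0.10 × 484 = 48.4, and 48.4 / (1 − 0.20) = 60.5. Starting from 48, 48 / 0.80 = 60. The target of 60 is reproduced.
- The inputs behind 484 are not given, but nothing here depends on them.

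**Who is reached**
- Per arm: 60 / 4 = 15. Exercise arms: 3 × 15 = 45.
- Controls outside both instruments by stated design: 15 / 60 = 25%.
- Exercise-arm women lost, if attrition is equal across arms: 0.20 × 45 = 9, leaving 36.
- Interviews: 18 / 45 = 40% of exercise-arm women, and 0 of 15 controls.

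| Items | Women concerned | Reached if invitation does not depend on follow-up | Reached if it does |
|---|---|---|---|
| Trial procedures, randomisation | 60 | 45 (75%) | 36 (60%) |
| Exercise programmes | 45 | 45 (100%) | 36 (80%) |

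These counts assume that every woman reached responds.

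**What the unreached women could change**

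With no assumption about their views, a percentage can vary by the unreached fraction. For procedure items that is 15 / 60 = 25 points, or 24 / 60 = 40 points if women lost to follow-up are also missed. For programme items it is 0 or 9 / 45 = 20 points. These are logical limits, not estimates.

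**Illustration of possible bias (assumed rates; the documents give none)**

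Overstatement = missing fraction × (rate among those reached − rate among those missed).
- Programme items, 20% missed, 90% of completers favourable: 0.20 × (0.90 − 0.50) = 8 points; 0.20 × (0.90 − 0.30) = 12 points.
- Same rates with 10% missed: 4 to 6 points. With 30% missed: 12 to 18 points.
- Equal rates: 0. If 80% of completers and 90% of those lost are favourable: 0.20 × (0.80 − 0.90) = −2 points.
- Randomisation items, controls missed, 90% favourable in exercise arms: 0.25 × (0.90 − 0.60) = 7.5 points; 0.25 × (0.90 − 0.75) = 3.75 points; equal rates give 0.

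The sign and size therefore depend entirely on rates that are unknown.

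**The case against.** The leading aim concerns the three exercise interventions, and for those the exercise arms are the right frame. Controls receive no programme during the 12 weeks, so their absence cannot distort acceptability of the programmes. Exercise-arm women also go through consent, randomisation and both assessments, so procedures are not wholly uncovered. All of this stands, and it limits the control-arm point to randomisation, assessments and the control allocation. It does not remove the point, since no exercise-arm woman can report what being a control was like.

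A reader might infer that dropouts are excluded. The text does not say so. The frame is defined by randomisation, and Follow-up assessment says that all participants are approached, so a woman who stops training but attends is inside it. The timing clause may also govern only the interview. Contact after withdrawal could be set out in a fuller protocol. What remains is an ambiguity that needs a clarifying sentence.

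A reader might also infer that a programme which drives women out would go unnoticed. Statistical methods reports retention, losses to follow-up, attendance, adherence and adverse events, so the losses would be seen. What may be missing is the reasons.

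Finally, a reader might contrast 100% favourable among 36 respondents with 60% over all 60 women. The plan contains no single acceptability percentage, the lower figure requires every unreached woman to be unfavourable, and 60 is the wrong denominator for programme items. The contrast is not a prediction.

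The condensed-article defence does not cover the controls. Their exclusion follows from a stated frame and a stated interview quota, not from silence.

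**Conclusion.** The point holds in two parts of unequal strength.

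- **Controls: firm.** By stated design, 15 of 60 women (25%) contribute nothing to a component of the main outcome that concerns them directly. This rests only on equal allocation and the target of 60.
- **Women lost to follow-up: qualified.** About 9 of 45 exercise-arm women have no described route to either instrument if follow-up completion is the trigger. This assumes that the 20% planning allowance applies equally across arms and that all attrition means a missed follow-up. Nine is not a maximum.

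It is plausible that acceptability will look better than it is. An established upward bias is not supported, because the documents give no rates by arm or completion status.

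**What to change.** 1. Send controls a version of the exit questionnaire on randomisation, assessments and waiting, at week 12 and before they start any offered programme.
2. Open interviews to some controls within the planned interview effort. No fixed quota is needed.
3. State that exercise-arm women receive the questionnaire and interview invitation at withdrawal or week 12, whichever comes first.
4. Report numbers invited and responding by arm and completion status. Use all randomised women as the frame for trial-procedure items and exercise-arm women only for programme items.

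The cost is a short extra questionnaire for about 15 women (controls only) to 24 (15 + 9, with those lost to follow-up), plus a minor ethics amendment. The instrument already exists and needs only adapting.
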